### Outcome measures

The primary efficacy endpoint is an ADHD Rating Scale (ADHD-RS) [37] score at 12 and 24 weeks. We will measure the different scores between the waiting group (group 3) and the CBT group (group 2) at 12 weeks to prove the effect of 12 weeks CBT on adult ADHD, and between the CBT with booster sessions (group 1) and the CBT group (group 2) at 24 weeks to explore the effect of booster sessions.

The main secondary endpoints will include the following:ADHD symptoms (Conners Adult ADHD Rating Scale Self-report Screening Version [38]) at 2, 3, 4, 5, 6, 7, 8, 9, 10, 11, 36, 48 weeksEmotional symptomatology (Self-rating Anxiety Scale [39], Self-rating Depression Scale [40]) at 2, 3, 4, 5, 6, 7, 8, 9, 10, 11, 12, 24, 36, 48 weeksExecutive function (Behavior Rating Inventory of Executive Function-Adult Version (BRIEF-A) [41], Cambridge Neuropsychological Testing Automated Battery (CANTAB) [42] at 12, 24, 48 weeksImpulsiveness (Barratt impulsiveness scale [43]) at 12, 24, 48 weeksSelf-esteem (self-esteem scale [44]) at 12, 24, 48 weeksLife quality (World Health Organization Quality of Life-Brief Version [45]) at 12, 24, 48 weeksNeuroimaging (Brain Oxygenation Level Dependent Signal) at 12 weeks.

We summarized the tools and the assessing time points in Table 1. The reasons we used these instruments to measure the efficacy are explained below. Since the ADHD symptoms are the main target of treatment and this manual was specifically designed for ADHD, the measurement of core ADHD symptoms is significant for confirming the effect of CBT. And the level of impulsiveness may manifest the core impairment of ADHD [46]. It was reported that emotional disorders were common for adult ADHD as comorbidities (the lifetime comorbid rates were 19.4% for generalized anxiety disorder and 28% for major depression [47]) and 32% of ADHD adults had emotional dysregulation [48], which makes it important to monitor the change of emotion during the intervention. Furthermore, the latest meta-analysis proved that CBT was effective for depression and anxiety [49], so the emotional results would be positive. The executive function of ADHD adults was reported to be impaired [50], and the BRIEF-A and the CANTAB could test both the ecological and practical aspect [51]. Moreover, the levels of self-esteem and life quality of ADHD adults were also proven to be lower than those of normal controls [52,53]. Additionally, the neuroimaging method as well as the neuropsychological tests could help identify the potential endophenotypic biomarkers that reflect or predict the outcomes of CBT, which would provide a strong evidence of the efficacy of psychotherapy [29]. Given the main consideration of core symptoms and the relatively great change of emotion [12,18,19], these were tested frequently. Furthermore, other aspects were evaluated, as done in previous studies [12-16,27], at three main endpoints, which were before treatment, after CBT and after booster sessions, whereas imaging was conducted at the end of 12 weeks because the efficacy of 12 weeks of CBT on brain functions had not been tested in adult ADHD as had been done in other studies [54,55].

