The booster sessions are designed according to the definition of booster sessions in studies of ADHD [13,14,27] and other diseases [21-25], the main goal of which is consolidating the skills learned and developing strategies dealing with recurrence or relapse. Thus, the booster sessions in the present study contain the induction of the first three parts above and practicing activities based on the patients’ questions in the real world. The first booster session includes a summary of the first organizational part of the 12-week manual. It also includes other important time-management skills such as goal setting, reward system and authorizing others [34], and a discussion of the practice questions through role-play. The second booster session consists of the summary of the distractibility part, the discussion of the relationship between distractibility and procrastination, and making a self-coping list. The last booster session includes a summary of the cognition part, the discussion of automatic thoughts of real situation by role-play, and the relationship between automatic thoughts and procrastination. These three booster sessions are conducted monthly after the complement of 12 weeks of CBT.

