### Blinding and quality control

There is an independent statistician who conducts the randomization of patients and analyzes the research results. The participants and endpoint assessors are kept blind during the study. Only the principal investigator is informed of the randomization results at first, and the psychotherapists are told when the 12 weeks of CBT is completed.

There are two psychiatrists who conduct the CBT and they have received same systematic psychotherapy training, including CBT training. They received psychological training courses held by the Peking University Sixth Hospital and the Chinese Psychological Society. One psychiatrist is in charge of the therapy, and the other is the recorder who writes down all the sessions. There also are two supervisors, including a psychiatrist and a psychotherapist. Regular discussion and supervision are conducted during the study. The assessors are mainly postgraduate students of psychiatry, and they are trained to use all the measurement tools and the consistency is rated.

The principal investigator monitors the research progress and ensures all the steps are taken according the original protocol, and the Ethics Committee supervises the interests of subjects such as safety and confidentiality.

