### Statistical analysis

The main analysis is a two-group ANCOVA of ADHD symptoms, emotional symptomatology, executive function, impulsiveness, self-esteem and life quality at all time points with baseline scores as covariates. To estimate the changes with time in every group, the repeated measures ANOVA will also be used. Furthermore, the neuroimaging data will be analyzed based on a voxel-by-voxel method and the general linear model with a one group by two time points design after pre-processing procedures. The statistics is based on intent-to-treat (ITT) analysis, and the last observation carried forward (LOCF) will be used to address the missing data.

The primary endpoints analysis is ANCOVA with ADHD-RS scores at 12 and 24 weeks separately as dependent variables and baseline ADHD-RS scores as covariates. Other variables that have correlation with ADHD-RS scores and clinical meanings will also be considered for covariates such as gender, age, IQ and education.

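### Groups 1 and 2 receive the same CBT until week 12, but the primary analyses leave group 1 out at week 12 and name only the baseline score as score covariate at week 24: an inefficiency, not a bias

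*Protocol article*

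**What the plan says.** All references are to the protocol article.

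- **When the arms diverge.** Both CBT groups receive the 12 weekly sessions (Study design; Intervention). Only group 1 goes on to boosters: "These three booster sessions are conducted monthly after the complement of 12 weeks of CBT".
- **Who knows the allocation.** Blinding and quality control describes participants and endpoint assessors as blind, and says "the psychotherapists are told when the 12 weeks of CBT is completed".
- **Week-12 contrast.** Outcome measures fixes it as "between the waiting group (group 3) and the CBT group (group 2) at 12 weeks to prove the effect of 12 weeks CBT". Group 1 takes no part.
- **Week-24 contrast.** The same section fixes it as "between the CBT with booster sessions (group 1) and the CBT group (group 2) at 24 weeks to explore the effect of booster sessions".
- **Model.** Statistical analysis says "The main analysis is a two-group ANCOVA", and for the primary endpoints "ANCOVA with ADHD-RS scores at 12 and 24 weeks separately as dependent variables and baseline ADHD-RS scores as covariates". Further variables "will also be considered for covariates such as gender, age, IQ and education"; the examples are all baseline characteristics. Missing data are filled by LOCF.
- **Data available.** Table 1 schedules ADHD-RS at baseline, weeks 2 to 11, week 12 and week 24. Table 2 gives batch sizes for groups 1/2/3 of 7/7/7, 8/8/8 and 14/14/none.

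**The concern.** Until the boosters begin, groups 1 and 2 are two random samples of patients on one treatment. Two things follow.

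First, group 1's week-12 scores bear on whether 12 weeks of CBT works as directly as group 2's do, yet they are not used. Meanwhile the planned contrast takes in 14 group 2 patients from batch 3, for whom no waiting patients were randomised. Pooling would allow that comparison to be limited to batches with a waiting arm without losing precision.

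Second, for the booster question the week-12 ADHD-RS is measured before the treatments differ. It can therefore serve as a pre-intervention covariate, and it will probably predict week 24 better than a score taken 24 weeks earlier. The booster comparison is the trial's novel question and has 29 patients per arm, so precision there is worth having.

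**Working it through.** **Inputs.** Arm and batch sizes are from Table 2. Pilot values are from Power: 29.80 ± 7.67 (n = 15) at baseline, 17.22 ± 7.62 (n = 18) after CBT, 10.56 ± 4.98 (n = 16) after boosters, 10% dropout, alpha 5%. The pilot differences are 29.80 − 17.22 = 12.58 and 17.22 − 10.56 = 6.66. The pooled SD of the first two time points is √[(14 × 7.67² + 17 × 7.62²)/31] = 7.64. Power is two-sided, by the noncentral t distribution.

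**The plan's own figure.** The article gives no standard error for either contrast, only arm sizes of 15, 29 and 29. Its formula with these inputs gives 6 per arm (7 with dropout) for 12.58 and 21 per arm (24 with dropout) for 6.66, so those sizes do not reproduce. That is a separate matter and nothing below depends on it.

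**Week 12.** The SE in SD units is √(1/n₁ + 1/n₂). Power is without dropout and without covariate adjustment. The 5- and 8-point differences are assumptions.

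| Comparison | SE factor | Power at 12.58 | at 8 | at 5 |
|---|---|---|---|---|
| Group 2 v 3, as planned, 29 v 15 | √(1/29 + 1/15) = 0.318 | 0.999 | 0.895 | 0.520 |
| Group 2 v 3, batches 1-2, 15 v 15 | √(1/15 + 1/15) = 0.365 | 0.992 | 0.790 | 0.409 |
| Groups 1+2 v 3, batches 1-2, 30 v 15 | √(1/30 + 1/15) = 0.316 | 0.999 | 0.899 | 0.525 |
| Groups 1+2 v 3, all batches, 58 v 15 | √(1/58 + 1/15) = 0.290 | above 0.999 | 0.946 | 0.606 |

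- Pooled concurrent against the plan: 0.316/0.318 = 0.994, so the same precision.
- Pooled concurrent against concurrent-only group 2 v 3: 0.316/0.365 = 0.866, an SE 13% lower.
- All batches against the plan: 0.290/0.318 = 0.911, an SE at most about 9% lower. This is before batch adjustment. With batch as a fixed factor, batch 3 has no waiting patients and adds nothing to the contrast. The variance factors are then 14/3 for batch 1 (1/(1/14 + 1/7)) and 16/3 for batch 2, total 10, so the SE factor is √(1/10) = 0.316 again.

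**Week 24.** Let a, b and c be the correlations of weeks 0-24, 12-24 and 0-12. Residual variance is proportional to 1 − a² with baseline alone. With both scores it is 1 − R², where R² = (a² + b² − 2abc)/(1 − c²). The documents give no correlations, so I assume a from 0.3 to 0.5, b from 0.5 to 0.7 and c from 0.4 to 0.6.

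- Most favourable corner (a = 0.3, b = 0.7, c = 0.6): R² = (0.09 + 0.49 − 0.252)/0.64 = 0.5125; ratio 0.4875/0.91 = 0.536. Residual variance falls 46%.
- Least favourable corner (a = 0.5, b = 0.5, c = 0.6): R² = (0.25 + 0.25 − 0.30)/0.64 = 0.3125; ratio 0.6875/0.75 = 0.917. Residual variance falls 8%.

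With 26 completers per arm (29 × 0.9 = 26.1) and SD 7.62, power at an assumed 5 points rises from 0.68 to 0.91 in the first case and from 0.76 to 0.80 in the second. At the pilot's 6.66 points it rises from 0.90 to 0.99 and from 0.95 to 0.96.

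**LOCF.** If a patient leaves before week 12, LOCF puts the same carried-forward value into the week-12 covariate and the week-24 outcome. Their correlation is then perfect by construction, so the new covariate cannot simply be added to LOCF-filled data.

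**The case against.** The strongest reply is that both planned contrasts are legitimate randomised comparisons that match the stated hypotheses, and that omitting group 1 or the week-12 score biases neither. That stands: this is a matter of efficiency.

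A reader might infer from the 15 v 15 row that pooling narrows the planned week-12 interval by 13% and lifts power at 8 points from 79% to 90%. The documents do not support that. The plan is 29 v 15, and against it the concurrent pool changes power at 8 points only from 0.895 to 0.899.

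Power at the pilot difference of 12.58 is already about 0.99 or more. This also stands, but that figure is an uncontrolled before-after change, and the article's Limitations section itself raises a placebo effect. Precision matters if the controlled effect is smaller, for example the assumed 5 to 8 points.

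The covariate list is open-ended, and a SAP may settle it. However, the score covariate that the article states is baseline, and its other examples are baseline traits.

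Finally, the week-12 score is measured after randomisation, and the article does not say that the week-12 rating comes before therapists learn the allocation. This is a fair condition on the fix and is built into it.

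**Conclusion.** The point holds as an inefficiency that should be corrected. At week 12 the benefit is a fully concurrent comparison at no loss of precision against the plan, since the 14 group 2 patients of batch 3 are no longer needed. Using all 58 CBT patients could lower the SE by at most about 9%, and batch adjustment removes most or all of that. At week 24 the direction of the gain is clear, but its size is uncertain: about 8% to 46% less residual variance over correlations that are assumed.

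Both parts rest on identical treatment, and on status as group 1 or group 2 staying concealed until the week-12 rating is done. A reader might conclude that the planned analyses are invalid; nothing in the article supports that on this ground.

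**What to change.** **Week 12.** Make the primary contrast groups 1+2 v group 3 within batches 1-2, by ANCOVA adjusting for baseline ADHD-RS and batch. Keep group 2 v group 3 as a sensitivity analysis. If all batches are pooled instead, adjust for batch and do not count on the 9%.

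**Week 24.** Compare group 1 with group 2 adjusting for baseline ADHD-RS, week-12 ADHD-RS and batch. Fit this as a longitudinal model of the observed scores, with the two arms sharing common means at baseline and week 12, so that patients without a week-12 score still contribute. Do not fit it on LOCF-filled scores. Keep the baseline-only ANCOVA as a sensitivity analysis.

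**Condition.** State that the week-12 rating is completed before allocation between groups 1 and 2 is disclosed to therapists, patients or assessors.

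**Cost.** No new data, visits or patients. The week-12 part is a wording change. The week-24 part also replaces the LOCF rule for that analysis, which is more than wording. Both should be fixed before anyone sees outcomes by group. The small downside is the reliance on concealment to week 12, which the two sensitivity analyses help to check.

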**Table 1 Tab1:** **Instruments applied at different time points**

**Instruments**	**Baseline**	**Week 2 to 11**	**Week 12**	**Week 24**	**Week 36**	**Week 48**
ADHD-RS	×	×	×	×	×	×
CAARS	×	×	×	×	×	×
SAS	×	×	×	×	×	×
SDS	×	×	×	×	×	×
BRIEF-A	×		×	×		×
CANTAB	×		×			
BIS	×		×	×		×
SES	×		×	×		×
WHOQOL-BRIEF	×		×	×		×
fMRI	×		×			

ADHD-RS, ADHD Rating Scale; CAARS, Conners Adult ADHD Rating Scale Self-report Screening Version; SAS, Self-rating Anxiety Scale; SDS, Self-rating Depression Scale; BRIEF-A, Behavior Rating Inventory of Executive Function-Adult Version; CANTAB, Cambridge Neuropsychological Test Automatic Battery; BIS, Barratt impulsiveness scale; SES, self-esteem scale; WHOQOL-BRIEF, World Health Organization Quality of Life-Brief Version; fMRI, functional magnetic resonance imaging.

### Blinding and quality control

There is an independent statistician who conducts the randomization of patients and analyzes the research results. The participants and endpoint assessors are kept blind during the study. Only the principal investigator is informed of the randomization results at first, and the psychotherapists are told when the 12 weeks of CBT is completed.

There are two psychiatrists who conduct the CBT and they have received same systematic psychotherapy training, including CBT training. They received psychological training courses held by the Peking University Sixth Hospital and the Chinese Psychological Society. One psychiatrist is in charge of the therapy, and the other is the recorder who writes down all the sessions. There also are two supervisors, including a psychiatrist and a psychotherapist. Regular discussion and supervision are conducted during the study. The assessors are mainly postgraduate students of psychiatry, and they are trained to use all the measurement tools and the consistency is rated.

The principal investigator monitors the research progress and ensures all the steps are taken according the original protocol, and the Ethics Committee supervises the interests of subjects such as safety and confidentiality.

### Power

It is a noninferiority randomized controlled study, and the primary outcome measure is the mean difference of the ADHD-RS scores between groups. Since there was no relevant study that included booster sessions for adult ADHD, we used the results of a self-controlled preliminary experimental study. At baseline, the score of the ADHD rating scale was 29.80 ± 7.67 (n = 15), after CBT the score was 17.22 ± 7.62 (n = 18), and after booster sessions the score was 10.56 ± 4.98 (n = 16). We assume the drop-out rate is 10%, because the previous studies showed good compliance, and the outpatients are willing to participate [18,19]. So with the power of 80% and alpha of 5% and based on the formula (n = 2[(tα + tβ)*σ/δ]^2, n means number of subjects, tα means t value of alpha, tβ means t value of beta, σ means population standard deviation, δ means deviation), the sample size is about 73 subjects including 15 patients in the waiting group (group 3), 29 in the CBT group (group 2), and 29 in the CBT with booster sessions group (group 1). The numbers of subjects varied in the three groups since the deviations (δ) of ADHD-RS scores after 12 week CBT and after booster sessions were different. Considering the real situation with recruitment, we separated it into three batches, with a total of 21, 24 and 28 subjects for one time (Table 2).

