### Limitations

The exclusion of several comorbidities might narrow the scope of application of the results since comorbidity is common for adult ADHD patients and may reflect a more severe condition. Furthermore, the recruitment of patients from a single research center could also influence the sample representatives.

The design of the waiting group could not fully reflect the effect of intervention by comparison since the placebo effect could also play a role. So a control group with non-directive activities, such as group discussion and psychoeducation, might be more comparable. With the limitation of staff and resources in a single center, this strategy could be used in multicenter research.

The follow-up time in this study is 48 weeks (1 year), which could be insufficient for testifying to the prolonged effect of booster sessions. As the participants are outpatients, we would get the consent of subjects to allow future contact and follow-up.

The dropping-out rate might be a little optimistic based on the data of our group’s previous studies. Since this study is funded and conducted in consecutive years, the sample could be more than we estimated.

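### The group sizes of 15 and 29 do not follow from the printed formula and pilot values, and the 80% power rests on uncontrolled before-after changes

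*Protocol article*

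**What the plan says.** The Power section of the protocol article sets the sizes "with the power of 80% and alpha of 5"%, using the formula "n = 2[(tα + tβ)*σ/δ]^2" and a 10% drop-out rate. For its planning values it says "we used the results of a self-controlled preliminary experimental study". It reports three pilot results:

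- Baseline: "the score of the ADHD rating scale was 29.80 ± 7.67 (n = 15").
- After 12 weeks of CBT: "after CBT the score was 17.22 ± 7.62 (n = 18").
- After boosters: "after booster sessions the score was 10.56 ± 4.98 (n = 16").

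The result is that "the sample size is about 73 subjects including 15 patients in the waiting group (group 3), 29 in the CBT group (group 2"), with 29 also in the CBT-plus-booster group. The section explains the unequal sizes by the two comparisons having different δ. It prints no numerical δ or σ and does not say whether alpha is one- or two-sided.

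The Outcome measures section defines both primary contrasts between randomized groups: waiting v CBT at week 12, and CBT plus booster v CBT at week 24.

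**The concern.** There are two faults. First, the article prints a formula, inputs and an answer, and the answer does not come out of the formula. Second, the only differences that the pilot offers are changes over time in treated patients, whereas the trial tests differences between randomized arms. Using the one for the other assumes that waiting patients do not change over 12 weeks, and that CBT-only patients do not change from week 12 to week 24.

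At stake is what the 80% figure means when the trial is read. The booster comparison is the novel question, and a null result at week 24 would naturally be judged against the stated power.

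**Working it through.** **Inputs (Power section).** Means 29.80, 17.22 and 10.56; SDs 7.67, 7.62 and 4.98; power 80%; alpha 5%; drop-out 10%. Inferred, because not printed: δ = 29.80 − 17.22 = 12.58 for CBT v waiting, and δ = 17.22 − 10.56 = 6.66 for booster v CBT. Alpha is taken as two-sided; one-sided makes every n smaller. The section calls the trial noninferiority but gives no margin, so no margin can enter the formula.

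**Step 1: try to reproduce 15 and 29.** With normal quantiles, n per group = 2[(1.96 + 0.842)σ/δ]².

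| Comparison | δ | σ | n | Rounded up | With 10% drop-out (÷ 0.9) | Stated |
|---|---|---|---|---|---|---|
| CBT v waiting | 12.58 | 7.67 | 5.84 | 6 | 7 | 15 |
| Booster v CBT | 6.66 | 7.62 | 20.55 | 21 | 24 | 29 |
| Booster v CBT | 6.66 | 6.44 | 14.66 | 15 | 17 | 29 |

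Here 6.44 = √[(7.62² + 4.98²)/2]. Using the t distribution adds about one patient per group.

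**Step 2: a check free of alpha, power and drop-out.** With normal quantiles and before rounding, these cancel from the ratio of the two sizes. With a common σ the ratio is (12.58/6.66)² = 3.57. With a separate root-mean-square SD for each comparison it is 2.53. The stated ratio is 29/15 = 1.93.

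**Step 3: near misses.**

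- One-sided 5%, t version, drop-out included, and n read as the total of both groups: 14 and 29. These totals would then have been used as group sizes, although a formula with the factor 2 gives n per group.
- σ = √(SD₁² + SD₂²), which counts the variance twice: σ = 9.10 gives 29.3 for the booster comparison before drop-out, but the matching figure for CBT v waiting (σ = 10.81) is 11.6. The t version gives 13 and 31 without drop-out, and 15 and 35 with it.
- Alpha 2.5% with 90% power, t version with drop-out: 13 and 28 to 29. This departs from both stated settings.

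No ordinary choice of SD, sidedness or drop-out, at the stated alpha and power, gives both 15 and 29.

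**Step 4: power of the stated sizes.** After 10% loss, 29 × 0.9 = 26.1, taken as 26, and 15 × 0.9 = 13.5, taken as 13. Power is for a two-sided 5% unadjusted t-test (noncentral t). The fractions below 100% are assumptions; the article gives no estimate of control-arm change.

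| True difference as share of pilot change | Week 12, 26 v 13 (SD 7.67) | Week 24, 26 v 26 (SD 7.62 to 6.44) |
|---|---|---|
| 100% (12.58; 6.66) | 99.7% | 87 to 96% |
| 75% (9.44; 5.00) | 94% | 64 to 78% |
| 50% (6.29; 3.33) | 65% | 34 to 45% |

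**Step 5: differences detectable with 80% power, unadjusted.** For 26 v 26, about 6.0 points (SD 7.62) or 5.1 points (SD 6.44). For 26 v 13, about 7.5 points (SD 7.67).

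**The case against.** Most of the opposing case concerns how far the point reaches, and much of it stands.

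- *The error is on the safe side.* True. A reader might infer from the failed arithmetic that the trial is too small. The article does not support that: the formula asks for fewer patients than planned. Low power arises only if the true between-group difference is well below the pilot change, and how far below is an assumption.
- *Control-arm change could go either way.* True for the booster comparison. The Background reports that treated patients forgot their skills, so CBT-only patients might worsen after week 12 and the true difference might exceed 6.66. That still leaves zero change unsupported.
- *The inputs are partly inferred.* True. No δ, σ or sidedness is printed, and n is defined only as the number of subjects. The inferred values are the only ones that the section offers, and the two-group-total reading does not rescue sizes then applied per group.
- *The planned analysis is a baseline-adjusted ANCOVA.* True, so the figures in Steps 4 and 5 are unadjusted. No baseline correlation is given. If it were 0.5 (assumption), the SD would shrink by √(1 − 0.25) = 0.866. The detectable differences would become about 5.2 (from 6.04) and 6.5 points, and power at 6.29 points would be about 77%.
- *The pilot is openly called self-controlled.* True, and the Background calls this evidence preliminary. What is not disclosed is that its within-group changes serve as between-group differences.

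A reader might also take the pilot counts of 15, 18 and 16 to prove that different patients were measured each time. They show only that different numbers contributed; one cohort with missing scores would look the same.

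**Conclusion.** Wrong as written. The sizes 15 and 29 do not follow from the printed formula and pilot values, which give about 6 (7 with drop-out) and 15 to 21 (17 to 24 with drop-out) per group. Taken alone, that error leaves no comparison short of patients. The 80% figure is nevertheless unsupported, because no between-group estimate lies behind it. The exposure is greatest for the booster contrast, where unadjusted power drops below 80% once the true difference is 75% of the pilot change. These conclusions rest on the inferred δ of 12.58 and 6.66, two-sided 5%, SDs between 6.44 and 7.67, and 10% loss.

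**What to change.** In the Power section, delete the statement that 15 and 29 result from the formula. State that the pilot values are within-group changes and not estimates of the between-group effects. Justify the existing 73 patients with wording such as:

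> After 10% loss, 26 v 26 gives 80% power (two-sided 5%, unadjusted) for a between-group difference of about 6.0 points on the ADHD-RS (SD 7.62; 5.1 points with SD 6.44), and 26 v 13 for about 7.5 points (SD 7.67). Baseline-adjusted ANCOVA may improve on this.

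Add the power range under partial control-arm change from Step 4, marked as an assumption. A short argument for why differences of this size are plausible and matter would make the statement a planning claim and not only a back-calculation.

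Cost: protocol wording and a less favourable power statement. No extra patients and no change to the design.

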**Table 2 Tab2:** **Numbers of subjects in three batches of the study**

**Batch**	**Group 1**	**Group 2**	**Group 3**	**Total**
1	7	7	7	21
2	8	8	8	24
3	14	14	-	28
Total	29	29	15	73

Group 1: Cognitive behavioral therapy (CBT) with booster sessions group; Group 2: CBT group; Group 3: waiting group.

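### Batch 3 has no waiting arm, so 14 of the 29 CBT patients in the week-12 CBT-versus-waiting contrast lack concurrently randomised controls, and the stated ANCOVA does not account for batch

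*Protocol article*

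**What the plan says.** The Power section of the protocol article plans 15 waiting, 29 CBT and 29 CBT-with-booster patients, and explains that intake is split: "Considering the real situation with recruitment, we separated it into three batches, with a total of 21, 24 and 28 subjects for one time". The split by arm is given in Table 2, headed "Numbers of subjects in three batches of the study". Groups 1, 2 and 3 receive 7, 7 and 7 in batch 1, then 8, 8 and 8 in batch 2. In batch 3 groups 1 and 2 receive 14 each, and there is a dash for the waiting group.

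Outcome measures defines the first primary comparison as "between the waiting group (group 3) and the CBT group (group 2) at 12 weeks to prove the effect of 12 weeks CBT", with no restriction by batch. Statistical analysis gives the primary model as "ANCOVA with ADHD-RS scores at 12 and 24 weeks separately as dependent variables and baseline ADHD-RS scores as covariates". It adds that variables which correlate with ADHD-RS and have clinical meaning "will also be considered for covariates such as gender, age, IQ and education". On the analysis set it says "The statistics is based on intent-to-treat (ITT) analysis". Neither batch nor recruitment period is named in the article as a covariate, a stratum or a restriction.

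**The concern.** In batches 1 and 2 each patient could be allocated to CBT or to waiting, so comparing those arms within a batch is randomised. In batch 3 the chance of allocation to waiting was zero. If all of group 2 is set against all of group 3, the batch 3 patients are compared with people recruited in other rounds, and batch is partly confounded with arm. A difference between rounds in case mix, season or assessors would then be counted as an effect of CBT, except for the part that baseline ADHD-RS picks up.

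This is the trial's first primary question and its only comparison of CBT with no treatment. The Background section says the uncontrolled evidence from the group's own earlier work needs validation in a randomised study, so a partly non-randomised contrast weakens what the trial was set up to supply.

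**Working it through.** **Inputs.** From Table 2: batch sizes by arm. From Power: baseline 29.80 (SD 7.67), after CBT 17.22 (SD 7.62), dropout 10%, alpha 5%. Assumed, because the documents give no value: D, the shift in week-12 ADHD-RS between batch 3 and batches 1-2 that is unrelated to treatment and not removed by baseline adjustment. A range of 2 to 6 points is shown.

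**1. Table 2 adds up.** By row: 21 + 24 + 28 = 73. By column: 7 + 8 + 14 = 29 (groups 1 and 2) and 7 + 8 = 15 (group 3).

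**2. Share without concurrent controls.** In group 2, 14/29 = 0.483. The other 15 have 15 concurrent waiting patients.

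**3. Bias.** The group 2 mean carries D in 14 of its 29 patients and the group 3 mean carries none, so bias = (14/29) × D = 0.483 D.

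**4. Type I error.** Simulation with no treatment effect, SD 7.65 (the average of 7.67 and 7.62), two-sided 5% t-test, no baseline covariate, 100,000 runs:

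| D (assumed) | Bias, 29 v 15 | Rejection, 29 v 15 | Rejection, 15 v 15 from batches 1-2 |
|---|---|---|---|
| 0 | 0 | 5.0% | 5.0% |
| 2 | 0.97 | 6.6% | 5.0% |
| 4 | 1.93 | 11.1% | 5.1% |
| 6 | 2.90 | 18.7% | 4.9% |

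Shorter runs of the same simulation gave 18.2% to 19.2% in the last row, hence 18-19%. Baseline adjustment works in two directions. It removes any part of a shift already visible at baseline, but it also lowers the residual SD, so a given remaining D would weigh somewhat more.

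**5. Cost of a concurrent comparison**, at SD 7.67:
- All batches: SE = 7.67 × √(1/29 + 1/15) = 2.44.
- Batches 1-2 only: SE = 7.67 × √(1/15 + 1/15) = 2.80.
- All 44 patients with batch as a fixed factor (least squares on the Table 2 design): SE = 2.80. This equals the restricted analysis, because within batch 3 there is no CBT-versus-waiting difference to estimate.

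**6. Power** (two-sided 5%, noncentral t). The planned difference is 29.80 − 17.22 = 12.58.

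| True difference | 29 v 15 | 15 v 15 | 13 v 13 (after 10% dropout) |
|---|---|---|---|
| 12.58 | 0.999 | 0.991 | 0.980 |
| 8 | 0.893 | 0.787 | 0.723 |
| 6 | 0.671 | 0.543 | 0.482 |

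**7. Are the batches successive?** The article ties them to recruitment, and Trial status reports 66% randomised by June 2014. Since 0.66 × 73 = 48, and batches 1 and 2 total 45, this fits batches filled one after another. It is a reading of the text, not a statement in it.

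**The case against.** **The covariate list is open and the full analysis plan is not shown.** True: batch is not excluded, and the article never writes 29 versus 15. But the allocation table, the unrestricted contrast, the intention-to-treat rule and the baseline-only model are all stated, and together they lead to that comparison. Other variables enter only if they correlate with the outcome and have clinical meaning, and the examples are all patient characteristics. A design factor that changed the allocation ratio should not depend on such a screen.

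**Nothing shows that a shift exists.** This stands. There is one centre, one manual, one set of eligibility criteria, the same two supervised therapists, and trained assessors whose consistency is rated. D is wholly assumed, and D = 6 is nearly half the planned effect. Only about 48% of any shift that survives adjustment reaches the estimate. The loss of randomised comparability for 14 patients does not depend on D, but its consequence does.

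**Therapist experience and larger batch 3 groups.** A reader might count these as sources of false positives. They act through the delivery of CBT, so if CBT does nothing they cannot create a difference by that route. They change which effect is being estimated. Only shifts unrelated to treatment produce the error rates above.

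**The planned effect is large.** Also true. Taking off the largest bias shown leaves 12.58 − 2.90 = 9.68 points, about 4 standard errors of 2.44. However, 12.58 comes from an uncontrolled before-after pilot, and the size of the estimate matters as well as its significance.

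**Conclusion.** The point holds in a limited form. As written, the week-12 CBT-versus-waiting analysis takes 48% of its CBT arm from a batch with no waiting allocation, and the stated model does not account for batch. The bias is about 0.48D: roughly 1.0, 1.9 or 2.9 points for assumed shifts of 2, 4 or 6 points, with type I error of roughly 6.6%, 11% or 18-19%. These figures rest on the assumed D, an SD of 7.65, and the reading that batches are separate rounds in time.

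Two stronger inferences are not supported. The first is that the CBT result would be invalid: the documents give no evidence of drift, and a true effect near the planned size would survive the largest bias shown. The second is that the booster comparison is compromised too: groups 1 and 2 are equal in every batch (7:7, 8:8, 14:14), so a shift between batches cancels.

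**What to change.** State before the week-12 data are analysed that the primary group 2 versus group 3 ANCOVA includes batch as a fixed factor alongside baseline ADHD-RS. Basing that contrast on patients randomised in batches 1 and 2 is equivalent for this purpose. Report the all-batch comparison without batch as a labelled sensitivity analysis.

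This changes analysis wording only; recruitment and allocation stay as they are. The price is precision: the standard error rises from about 2.44 to 2.80 points at SD 7.67. Power at the planned 12.58 points remains about 0.99 (0.98 for 13 v 13 after dropout), but the loss is visible if the true effect is much smaller, for example 0.79 instead of 0.89 at 8 points.

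Including batch in the group 1 versus group 2 model is good practice because allocation is set by batch, but it is not needed to remove bias there.
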